#### **7.1.4 Subsequent 12-weekly visits (excluding “annual” visits and final trial visit)**

These visits are required for ***all patients***.

The visit windows are  $\pm 6$  weeks from the target visit date. There is no requirement for fasting or drug scheduling for these visits. The following assessments will be performed:

- Review of symptoms
- Review of concomitant medications
- Adherence to ART (no. of missed doses in previous 2 weeks and since last visit)
- Targeted physical examination (as needed to evaluate reported symptoms)
- Review of healthcare resource utilisation since last visit (patient self-report and review of case sheet)
- EQ-5D health status questionnaire (self-completed by patient)
- Laboratory tests:
  - HIV viral load
  - CD4+ count
  - Full blood count (haemoglobin, white cells, neutrophils, lymphocytes and platelets)
  - Biochemistry (sodium, potassium, urea, creatinine, bilirubin, ALT, alkaline phosphatase)
  - Bone profile (calcium and phosphate; only required for patients taking tenofovir)
  - Urine protein / creatinine ratio (only required for patients taking tenofovir)

#### **7.1.5 “Annual” visits (week 48, 96, 144, 192, 240) and final trial visit**

These visits are required for ***all patients***.

The visit windows are  $\pm 6$  weeks from the target visit date. Patients should be instructed to not eat or drink anything (except plain water) from midnight before the visit. The following assessments will be performed:

- Review of symptoms (including specific questions about neuropathy and body fat changes)
- Review of concomitant medications
- Adherence to ART (no. of missed doses in previous 2 weeks and 3 months)
- Targeted physical examination (as needed to evaluate reported symptoms; at this visit will include measurement of blood pressure, body weight, waist and hip-circumference and assessment of facial lipoatrophy; the final trial visit will also include an assessment of peripheral neuropathy)
- 10-year cardiovascular risk assessment
- Neurocognitive assessment
- Review of healthcare resource utilisation since last visit (patient self-report and review of case sheet)
- EQ-5D health status questionnaire (self-completed by patient)
- MOS-HIV quality of life questionnaire (self-completed by patient)
- Laboratory tests:
  - HIV viral load
  - CD4+ count
  - Full blood count (haemoglobin, white cells, neutrophils, lymphocytes and platelets)
  - Biochemistry (sodium, potassium, urea, creatinine, bilirubin, ALT, alkaline phosphatase)

- Bone profile (calcium and phosphate; required for all patients at this visit)
- Fasting glucose
- Fasting lipids (total cholesterol, triglycerides, LDL, HDL)
- Hepatitis B and C serology (if clinically indicated)
- Plasma storage (1x 4ml EDTA at annual visits; 2x 4ml EDTA at final trial visit)
- Urine protein / creatinine ratio (required for all patients at this visit)
- Urine storage

### **7.1.6 Additional visits for virological rebound**

These visits are required for ***all patients***.

In the event that the patient has a result of  $\geq 50$  copies/ml on the VL rebound original sample and on the VL rebound original sample repeat test (by a repeat laboratory test on the same sample or on a repeat sample taken within 4 weeks after the original sample), an additional visit will be required for a VL rebound confirmation sample. This should be scheduled to occur at 4-8 weeks following the date that the VL rebound original sample was obtained (see section 7.2.1).

#### ***VL rebound confirmation visit***

For this repeat visit, patients in the PI monotherapy arm should be instructed not to take their morning dose of PI medication (other medications can be taken) until after the blood has been drawn. All other patients can take their morning medication as scheduled. The following assessments will be performed at this visit:

- Review of symptoms
- Review of concomitant medications
- Adherence to ART (no. of missed doses in previous 2 weeks and 3 months)
- Targeted physical examination (as needed to evaluate reported symptoms)
- Review of healthcare resource utilisation since last visit (patient self-report and review of case sheet)
- EQ-5D health status questionnaire (self-completed by patient)
- Laboratory tests:
  - HIV viral load
  - HIV viral load storage sample (for a VL rebound confirmation sample repeat test; only needed if a VL rebound original sample repeat test was not performed).
  - Resistance testing storage sample (for testing at the local laboratory; store until VL test result available and only proceed if  $\geq 50$  copies/ml on the VL rebound confirmation sample)
  - PIVOT plasma storage sample (2x 4ml EDTA sample for later batched tests which may include PI drug levels)
  - Additional tests as per trial schedule or if clinical indication

If the VL rebound confirmation sample test shows an undetectable VL, follow-up will resume according to the next routine visit in the trial schedule. If the VL rebound confirmation sample test shows a VL  $\geq 50$  copies/ml (and this is the 3rd consecutive VL  $\geq 50$  copies/ml), patients will be managed as described in section 6.2.2 and 6.3.4. Ordinarily, therapy will be changed at this point and patients will subsequently be managed as described in section 7.1.7 below. If the VL rebound confirmation test was only the second consecutive VL  $\geq 50$  copies/ml, then a VL rebound confirmation sample repeat test will need to be performed (either on the same sample or on a repeat sample drawn within 4 weeks, as described in section 7.2.1 below) prior to change of therapy. If therapy is continued unchanged in spite of 3 consecutive VL results with VL  $\geq 50$  copies/ml, an additional VL rebound visit will be arranged within 4 weeks.

### ***Additional VL rebound visits***

These visits will occur no less often than every 12 weeks in patients who continue to have VL  $\geq 50$  copies/ml. The visits will usually be arranged to coincide with routine visits in the trial schedule. An additional VL rebound visit must be performed at the time of change of therapy or within no more than 4 weeks prior to change of therapy, if therapy is changed for reasons of VL rebound. At these visits the following assessments will be performed:

- Review of symptoms
- Review of concomitant medications
- Adherence to ART (no. of missed doses in previous 2 weeks and 3 months)
- Targeted physical examination (as needed to evaluate reported symptoms)
- Review of healthcare resource utilisation since last visit (patient self-report and review of case sheet)
- EQ-5D health status questionnaire (self-completed by patient)
- Laboratory tests:
  - HIV viral load
  - Resistance testing (needed if more than 70 days have elapsed since the date of the last resistance test sample; store blood and only proceed if VL  $\geq 50$  copies/ml on this sample)
  - Plasma storage (1 x 4ml EDTA sample for later batched tests which may include PI drug levels)
  - Additional tests as per trial schedule or if clinical indication

If the additional VL rebound test shows undetectable VL, follow-up will resume according to the next routine visit in the trial schedule. If the additional VL rebound test shows a VL  $\geq 50$  copies/ml, patients will be managed as described in section 6.2.2 and 6.3.4. Ordinarily, therapy will be changed and patients will subsequently be managed as described in section 7.1.7 below. If therapy is continued unchanged, then subsequent additional VL rebound visits will be arranged at no less often than every 12 weeks (usually to coincide with routine visits in the trial schedule) until the patient changes treatment. When the patient eventually changes treatment, an additional visit will be arranged as described in section 7.1.7 below.

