#### 6.2.2 Virological monitoring and switching strategy

Patients in the triple therapy arm will have VL testing performed every 12 weeks during the study (see trial schedule, section 1.3). In the event of VL rebound  $\geq 50$  copies/ml (verified on a second laboratory run using the original sample or a repeat sample drawn within 4 weeks of the original blood sample as described in section 7.2.1), the patient will be contacted by telephone, counselled on medication adherence, and asked to return for a repeat blood test after at least 4 weeks and if possible less than 8 weeks from the date of the first test. At the time of this VL rebound confirmation sample, additional blood samples will be taken for resistance testing (saved and performed only if VL  $\geq 50$  copies/ml on the rebound confirmation sample) and for PIVOT blood storage (2 X 4ml plasma samples) and for a VL rebound confirmation sample repeat test (only needed if the original sample repeat test was not performed). The assessments performed at this visit are described in section 7.1.6.

For the purposes of statistical analysis and clinical management in the PIVOT protocol, confirmed VL rebound is defined as 3 consecutive VL tests  $\geq 50$  copies/ml, with at least 4 weeks between the first and last test. One of these 3 tests may be a repeat of the same sample. Patients who develop confirmed VL rebound whilst taking triple therapy will ordinarily be expected to change therapy to a new optimised regimen, taking into account the results of any resistance tests performed. However the clinician and /or patient may elect to continue the current regimen without change if considered appropriate, and the reasons for not changing therapy will be documented on the case report form. A further VL must be obtained within 4 weeks (together with an additional 1 X 4ml sample for plasma storage) and if this remains detectable patients should change therapy.

If the clinician and/or patient choose to continue the triple therapy regimen, the reasons for not changing therapy will again be documented on the case report form. VL testing will be repeated at least as often as every 12 weeks (more often if clinically warranted). A blood sample for resistance testing and PIVOT plasma sample storage (1 X 4ml) will also be repeated every 12 weeks until VL suppression occurs spontaneously or treatment is changed.

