At the time of changing therapy a repeat sample will be sent for resistance testing and a PIVOT plasma sample will be taken (1 X 4ml) if these have not been performed in the 4-weeks prior to switching therapy.

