If the clinician and /or patient choose to continue the PI monotherapy regimen, the reasons for not restarting triple therapy will again be documented on the case report form. This should also be discussed with the chief investigator at MRC CTU. If the PI monotherapy is maintained, VL testing will be repeated at least as often as every 12 weeks (more often if clinically warranted). A blood sample for resistance testing and PIVOT plasma sample storage (1 X 4ml) will be repeated every 12 weeks until VL suppression occurs spontaneously or treatment is changed. At the time of changing therapy a repeat sample will be sent for resistance testing and a PIVOT plasma sample will be taken (1 X 4ml) if these have not been performed in the 4-weeks prior to switching therapy.

When a patient resumes triple therapy they will be managed exactly as for patients in the control arm, as described in section 6.2.

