### 7.2.3 Resistance testing

Drug resistance is the key component of the primary endpoint, and hence the detection of new resistance mutations needs to be pursued fastidiously in this trial.

All patients who have a VL rebound confirmation sample taken will have a number of additional blood samples drawn at the same time (see section 7.1.6), including a sample for storage for local genotypic resistance testing. Genotypic resistance testing will be performed on the sample if the VL confirmation result is  $\geq 50$  copies/ml. Resistance testing will be performed by the local laboratory that is normally used by the site. A designated referral laboratory, normally used by the site for performing resistance testing at low VL levels, may be used also. In the event that sequencing is unsuccessful, the sample stored for genotypic resistance testing will be transferred to the PIVOT storage samples and will be tested by the study central resistance laboratory at UCL/UCLH at the end of the study period. All the sequences will be analysed using the Stanford algorithm, and the level of resistance to individual drugs will be classified as none (susceptible), potential low level, low level, intermediate level, high level.

Comparison will be made with the drug resistance profile obtained from any other previous sequences available for that patient (pre-treatment resistance testing is commonly performed at most centres in the UK). If a patient develops virological rebound with resistance during the course of the trial but does not have a prior resistance test result for comparison, attempts will be made to identify a stored (pre-treatment) sample and if

available this sample will be tested to determine whether transmitted resistance was present prior to antiretroviral therapy.

As a further measure to make the best possible comparison of the two treatment strategies in terms of drug resistance development, selected stored samples from patients who have rebounded to a sufficiently high viral load (VL > 1000 copies/ml) will be tested using a minority species resistance assay at the end of the trial.

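### At a change of therapy for rebound, sections 6.2.2 and 6.3.4 want a new genotype if the last is over 4 weeks old; the 7.1.6 checklist asks for it only after 70 days, so it could be omitted

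*Combined protocol and SAP*

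**What the plan says.** For the triple-therapy arm, section 6.2.2 ends with the rule that a repeat sample goes for resistance testing when therapy is changed, "if these have not been performed in the 4-weeks prior to switching therapy". Section 6.3.4 states the same rule for the PI monotherapy arm: "At the time of changing therapy a repeat sample will be sent for resistance testing", with the same 4-week condition.

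Section 7.1.6, under the sub-heading on additional VL rebound visits, fixes the visit at which this would happen when the reason for the switch is rebound: "An additional VL rebound visit must be performed at the time of change of therapy or within no more than 4 weeks prior to change". One list of assessments then follows, introduced by "At these visits the following assessments will be performed". In that list, resistance testing is "needed if more than 70 days have elapsed since the date of the last resistance test sample". No separate condition is given for a visit held because of a switch.

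For patients who stay on a failing regimen, section 6.2.2 says: "A blood sample for resistance testing and PIVOT plasma sample storage (1 X 4ml) will also be repeated every 12 weeks". Section 7.2.3 calls drug resistance the key part of the primary endpoint and says "the detection of new resistance mutations needs to be pursued fastidiously in this trial".

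**The concern.** Two sets of instructions apply to the same visit and give different answers for some patients. A clinician reading the treatment sections would send a genotype. A site working through the visit checklist could conclude that none is due.

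The sample at the switch is the last one taken under the failing regimen. If the new regimen re-suppresses the virus, no later genotype is triggered, because testing proceeds only at 50 copies/ml or more, and the visit after the change (section 7.1.7) requires only a viral load. Resistance that appeared between the confirmation sample and the switch could then go unrecorded, and the patient could be counted as having kept all drug options. Sites following different sections would also be ascertaining the primary endpoint differently.

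**Working it through.** The plan states no figure to reproduce, so the check compares the rules and then asks which routes reach the conflict.

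**Inputs**
- Treatment sections 6.2.2 and 6.3.4: new sample if none in the last 4 weeks, i.e. 28 days.
- Checklist in 7.1.6: new sample if the last is more than 70 days old.
- Repeat testing on a continued failing regimen (6.2.2, 6.3.4): every 12 weeks, i.e. 84 days.
- Section 9.3: 277 per arm, 97% free of the endpoint at three years, 10-point margin, 24 months' uniform recruitment, 60 months' total duration.

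**Where the rules disagree**

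| Age of last genotype at the switch | 6.2.2 / 6.3.4 | 7.1.6 list |
|---|---|---|
| up to 28 days | not required | not required |
| 29 to 70 days | required | not listed as needed |
| over 70 days | required | required |

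The band is 70 − 28 = 42 days wide.

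**Routes into the band** (day 0 = genotype at the confirmation visit)
- *Ordinary route.* Therapy is changed on the confirmation result. A switch by day 28 falls under neither rule.
- *Confirmation sample repeated.* If the confirmation test is only the second consecutive raised value, section 7.2.1 requires a repeat, which may be a new draw up to 28 days later. A late draw plus time for the result passes day 28.
- *Regimen continued or PI altered after confirmation.* A further viral load is due within 4 weeks, with plasma storage but no stated genotype, and therapy should change if virus is still detectable. If each result takes t days, the switch falls between 2t and 2t + 28 days: days 14 to 42 for t = 7, and days 28 to 56 for t = 14. The documents do not give t.
- *Longer continuation with 12-weekly genotypes.* The band covers 42 of 84 days, or 50% of a cycle.

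These are ranges of possible dates, not shares of patients.

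**Whether another provision recovers the sample**
- Section 7.1.6 stores 4 ml of plasma at each additional rebound visit, for later batched tests, but mandates no resistance test on it.
- Central resistance testing (7.2.3, Appendix 11) is for samples whose local sequencing failed.
- The end-of-trial minority-species assay (7.2.3) covers selected samples above 1000 copies/ml.

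Recovery is therefore possible but not required.

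**Size of one missed event**
- As a simple proportion of an arm: 1/277 = 0.0036, or about 0.36 percentage points.
- For scale, the planned hazard is −ln(0.97)/3 = 0.0102 per year, and mean follow-up is (36 + 60)/2 = 48 months, or 4 years. Expected events per arm: 277 × (1 − exp(−0.0102 × 4)) ≈ 11.
- If the same fraction f of events were missed in both arms, the observed difference would be (1 − f) times the true one, i.e. closer to zero. The documents give no value for f.

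**The case against.** The strongest reply is that the rules can be read together. The 7.1.6 bullet says when a test is needed; it does not forbid one earlier. The same passage sends patients with detectable virus back to 6.2.2 and 6.3.4, where the 4-week rule sits, and the list allows extra tests on clinical indication. On this reading, 70 days serves the 12-weekly repeats and 4 weeks is an added trigger at a switch.

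That shows how the text may have been meant, but it does not settle what a site should do. The reference back concerns management once the viral load result is known, after the visit. The 70-day condition also governs whether blood for resistance testing is set aside, and nothing says the 4-week rule prevails.

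Other parts of the reply stand. The stricter rule is current text for both arms. Changing therapy at confirmation is described as the ordinary course, and altering the PI instead as exceptional. A lost event needs a switch in the band, a site that overlooks the treatment sections, qualifying resistance first arising in that interval, no later genotype, and no test of the stored plasma.

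Three stronger readings are tempting but unsupported:
- **That half of switches among continuing patients fall in the band.** This needs switch dates spread evenly over the 12 weeks. If switches follow soon after the 12-weekly genotypes, they fall outside it.
- **That resistance arising before the switch is lost for good.** Plasma from that visit is kept and could be sequenced.
- **That about 9% of an arm's events are at risk.** That figure is 1/11, the weight of a single event, not a forecast of how many are missed.

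**Conclusion.** The inconsistency is real, lies in current text, and concerns the visit that precedes or accompanies a change of therapy. For genotypes 29 to 70 days old at the switch, a site following 7.1.6 could omit a test that 6.2.2 and 6.3.4 require. Primary-endpoint resistance could be missed, and ascertainment could vary by site. Patients switched within 28 days of their last genotype are unaffected.

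The number of patients in the band cannot be derived from the documents, so neither can the number of missed events. Each would be about 0.36 percentage points of an arm, against a 10-point margin. A reader might infer that the non-inferiority conclusion is in danger. The documents do not support this: the 4-week wording is common to both arms, the 7.1.6 list applies to all patients, and nothing shows unequal loss. Equal proportional loss would pull the difference towards zero, a direction worth guarding against in a non-inferiority trial, but its size is unknown.

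Priority is moderate: the effect is unquantified and probably confined to a minority route, but it touches the primary endpoint and is cheap to remove.

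**What to change.** Reconcile sections 6.2.2, 6.3.4 and 7.1.6 so that one resistance-sampling rule applies at the change-of-therapy visit. One way is for the 7.1.6 bullet to carry the switch-visit condition already stated in the two treatment sections, keeping the 70-day condition for the 12-weekly repeats. The choice of interval belongs to the trial team, since resistance results also inform the next regimen.

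For endpoint ascertainment, add to the resistance-testing section and the analysis plan that, where a switch for rebound took place without that genotype, the plasma stored at that visit will be sequenced in the central laboratory before the primary analysis, under the same rule in both arms. Reporting by arm how many switches fell 29 to 70 days after the last genotype, and how many stored samples gave a sequence, would supply the size that cannot be worked out now.

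The cost is a one-line amendment, a sentence in the analysis plan, and what should be a small number of extra genotypes on plasma already stored. Some stored samples may not amplify at low viral load, so recovery may be incomplete.

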#### **7.1.7 Additional visits following ART change**

This visit is required for ***all patients***.

For patients in either treatment arm who change therapy as a result of VL rebound, an additional visit should be scheduled at 4-6 weeks following the date of therapy change. Review of symptoms, concomitant medication and treatment adherence will be performed. The only required laboratory assessment at this visit is VL testing, but additional laboratory tests may be performed as clinically indicated. Follow-up should then resume according to trial schedule, but further unscheduled visits may be arranged if considered appropriate for clinical management.

#### **7.1.8 Annual clinical notes review during the extension phase**

During the extension phase, the following data will be collected by annual retrospective review of the patients' routine clinic records:

- Changes in ART during the review period
- HIV viral load, latest CD4 count and creatinine results during the review period
- Resistance test results during the review period
- AIDS events, serious non-AIDS events or death during the review period

## 7.2 Procedures for assessing efficacy

### 7.2.1 Viral load

VL testing will be performed at the local site laboratory with the standard assay for detecting low levels of VL that is routinely used at the site. The site laboratory will be required to demonstrate satisfactory participation in a recognised quality control program for VL testing.

For the purposes of statistical analysis and for clinical management in the PIVOT study protocol, confirmed VL rebound is defined as 3 consecutive VL tests  $\geq 50$  copies/ml, with at least 4 weeks between the first and last test. One of the 3 tests may be a repeat of the same sample.

The procedure for documenting confirmed VL rebound is as follows. Any VL result  $\geq 50$  copies/ml will be initially verified by re-testing the **VL rebound original sample** on a separate laboratory run. If it is not possible to re-test the original sample, the patient should be called for a repeat blood test within four weeks from the date of the original sample. The re-test on the original sample, or on the repeat blood draw taken within 4 weeks, are regarded as equivalent and are termed the **VL rebound original sample repeat test**. If the result of the original sample repeat test is confirmed as  $\geq 50$  copies/ml, the patient will be recalled for a **VL rebound confirmation sample** that must be taken at least four (and if possible less than 8 weeks) after the date of the original sample. If an original sample repeat test was not performed, then it is essential for the PIVOT protocol that a **VL rebound confirmation sample repeat test** be performed. This confirmation sample repeat test can be done either by retesting the confirmation sample on a separate laboratory run, or by recalling the patient for a repeat blood test as soon as possible (and within four weeks from the date of the confirmation sample).

